## Abstract

**Background:**

The incidence of depressive symptoms increases during adolescence, from 10.0% to 24.5% at age 11 to 15, respectively. Experiencing elevated levels of depressive symptoms increases the risk of a depressive disorder in adulthood. A universal school-based depression prevention program Op Volle Kracht (OVK) was developed, based on the Penn Resiliency Program, aimed at preventing the increase of depressive symptoms during adolescence and enhancing positive development. In this study the effectiveness of OVK will be tested and possible mediators of program effects will be focus of study as well.

**Method:**

The effectiveness of OVK will be tested in a randomized controlled trial with two conditions, intervention (OVK) and control condition (care as usual). Schools are randomly assigned to research conditions. OVK will be incorporated in the school curriculum, maximizing program attendance. OVK consists of 16 lessons of 50 min, given by trained psychologists to groups of 11-15 students. OVK contains Cognitive Behavioral Therapy, social skills training, problem solving and decision making. Outcomes are measured at 6, 12, 18 and 24 months follow up, to monitor long term program effects. Primary outcome is level of depressive symptoms, secondary outcomes are: anxiety, hopelessness, cognitive bias, substance use, truancy, life satisfaction, coping, self-efficacy, optimism, happiness, friendship, school performance and school attitude. The questionnaires for students will be administered in the school setting. Parents will complete a questionnaire at baseline only.

**Discussion:**

In this paper the study into the effectiveness of the depression prevention program OVK was described. It is expected that OVK will prevent the increase in depressive symptoms during adolescence and enhance positive development in the intervention condition, compared to the control condition. If OVK will be effective, it can be implemented in the school context by which numerous adolescents can be reached.

**Trial registration:**

Netherlands Trial Register (NTR): NTR2879

## Background

Depression is a significant public health concern that places a heavy burden on people and society. In the Netherlands, around 700.000 adults and 37.000 adolescents (13-17 years) are diagnosed with a depressive disorder annually [1]. During adolescence, the incidence of both depressive symptoms and disorder increases [2-5]. At ages 9 to 10, 0.5% of all children suffer from a depressive disorder, which rises to 3.4% at ages 15 to 16 [6]. At age 11, 10.0% experience depressive symptoms, at age 15 this has increased up to 24.5% [7]. Symptoms of depressive disorder involve for example: loss of interest in activities, weight and sleep problems, negative thoughts about the self, and thoughts about death and harming the self [8]. Across adolescence, girls are twice as likely as boys to report depressive symptoms and are at greater risk for developing a depressive disorder compared to boys [5,7]. The risk for an episode of depressive disorder in adulthood sharply increases when having experienced elevated symptoms of depression during adolescence [9], or when diagnosed with depressive disorder during adolescence [10]. Depressive disorder often co-exists with anxiety disorder, conduct disorder, oppositional deviant disorder, and is related to substance use [11]. In addition, depressive disorder is often associated with impairments in adolescents' school, family and social functioning [12]. Moreover, depressive disorder is associated with high treatment costs [1,13]. To conclude, there is a strong urge to prevent the onset of symptoms of depression and depressive disorder during adolescence.

Besides preventing the onset of aversive outcomes, adolescent functioning and development could be enhanced by promoting positive development. The Broaden and Build Theory posits that when experiencing positive emotions, people's thoughts and subsequent actions are expanded by becoming more creative and diverse when compared to experiencing negative emotions [14]. By means of these broadened thoughts and actions, people encounter more learning experiences, which in turn facilitate people's cognitive, social, physiological, and psychological development. In addition, experiencing positive emotions can undo the cardiovascular arousal negative emotions cause, as described in the Undoing Hypothesis [15]. It is therefore important to promote positive emotions in enhancing youth development. The importance of prevention and promotion of positive development in adolescence is also stressed by parents, teachers, and school principles. Research has shown that universal social emotional programs resulted in an improvement of academic performance, social and emotional skills, and in a reduction of conduct and internalizing problems [16].

Early adolescence offers great opportunities for mental health promotion and the prevention of mental health problems. As the brain matures, young adolescents' social, emotional and cognitive systems are developing [17,18], and the behavioral and cognitive systems develop at different rates [18]. On the one hand this poses challenges for optimal functioning in adolescents, but on the other hand it provides great opportunities for mental health promotion. Considering that adolescents have not fully matured cognitively and emotionally, adolescence is a period in which cognitive biases, reactions to stress, and self-efficacy beliefs are malleable. This is important given that self-efficacy, coping with stress, and cognitive biases are strongly related to depressive disorder and related characteristics [19-21]. Addressing self-efficacy, coping, and cognitive biases in depression prevention programs could promote youths' mental health and decrease the incidence of depressive symptoms and depressive disorder in adolescence.

Research shows that universal depression prevention programs can be effective in reducing depressive symptoms in adolescents [22,23]. Stronger effects are found in targeted prevention compared to universal prevention, but in targeted prevention not all adolescents at risk are identified [24]. In universal prevention the stigmatization effect associated with targeted prevention is no issue [25], and all adolescents are reached. Various universal depression prevention programs exist [22], but up till now, no universal depression prevention program has been empirically tested and implemented in the Netherlands. To fulfill this need, 'Op Volle Kracht' (OVK) was developed. OVK is a universal school-based depression prevention program for adolescents aged 12 to 14, that targets, among others, cognitive biases, coping skills and social skills. The theoretical basis of OVK is Cognitive-Behavioral Theory (CBT) of which the attendant therapy is known to effectively combat depression in adults [26], and is promising in treating depression in adolescents [27]. OVK is an adapted version of the Penn Resiliency Program (PRP), a U.S. depression prevention program that has shown to effectively prevent and decrease depressive symptoms in adolescents [28]. Important cultural and content-related modifications have been made to make the program suitable for Dutch teenagers.

The present study will test the effectiveness of OVK in an adolescent Dutch population by means of a randomized controlled trial with follow-up assessments up to 24 months. In addition, mechanisms by which the program effects will be obtained will by studied as well. Scholars have tested the effectiveness of depression prevention programs [22,23]. The mechanisms underlying program effects are still unknown. Identifying mediating factors can increase our understanding of resiliency development in youth, and could provide directions for improvements of prevention programs. In the prevention program 'Op Volle Kracht', different aspects are targeted that might function as mediating mechanisms in accomplishing prevention of depression. Research has shown that adolescents showing cognitive biases are at risk for developing a depressive disorder [21]. Also, avoidant coping styles [29,30], low social and academic self-efficacy [19], and hopelessness are significant predictors of depressive symptoms in adolescents [31]. Optimism has a preventive function, as higher levels of optimism predicted lower levels of depressive symptoms in adults [32]. Hence, improving adolescents' cognitions, coping, self-efficacy, hopefulness and optimism may prevent the onset of depressive symptoms in adolescents and foster resilience.

### Goals and hypotheses

The present study has three main goals: 1) Testing the effects of OVK in a Dutch adolescent population in limiting the increase of depressive symptoms during adolescence, 2) identifying mediating mechanisms that can explain program effects, and 3) testing the effects of OVK on secondary outcomes. It is hypothesized that OVK will be effective in preventing the increase in depressive symptoms in adolescence in the intervention condition during the 24 months following the program, in comparison to the control condition. In relation to identifying mediating mechanisms, it is hypothesized that OVK will lead to less cognitive biases, more adequate coping, higher self-efficacy, less hopelessness, and more optimism. Each of these constructs are hypothesized to lead to less (increase in) depressive symptoms; being mediators of the program effects on depressive symptoms. Secondary outcomes include anxiety, substance use, truancy, life satisfaction, happiness, friendship, school performance and school attitude.

## Methods

### Design

The effectiveness of OVK will be studied by means of a randomized controlled trial with two conditions: intervention versus control (no intervention) (see Figure 1). We have chosen not to include a third condition with an alternative program, because there is no existing Dutch school-based universal depression prevention program for young adolescents, and because of financial constraints. Therefore, the control condition correctly reflects "care as usual". Randomization of schools, stratified by educational level, to either one of the conditions will be conducted by an independent statistician of the Radboud University. Stratifying by educational level is needed to evenly distribute educational level across intervention and control group, despite the small number of schools. Randomizing between schools (as opposed to within schools) will have the following benefits: It will minimizes contamination; adolescents in the control condition are not influenced by their friends in the experimental arm, and it will provide all adolescents in the second grade of a particular school with the opportunity to participate in the prevention program.

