### Participants and procedure

Participants will be adolescents in their second year of secondary school (8th grade, ages 12-14) [28]. Secondary schools in the southern and middle part of the Netherlands will be approached to participate in the study. Only adolescents in middle school grade 8 will be included. We will ensure inclusion of low SES and ethnic minority groups, as well as different educational levels (Dutch middle school prepares adolescents for vocational up to university level). The exclusion criterion consists of parental refusal of their child's participation in the study. When schools show interest, they will be asked to participate with as many as possible second grade classrooms. We expect that-once included in the study-across the entire study period, approximately 80% of adolescents will provide complete data [33,34].

A meta-analysis on 17 controlled studies on PRP indicated the significant average effect size to be 0.20 at 12-months follow-up with the CDI > 13 score as cut-off [28]. Power analysis (G-power) based on this 12-month mean effect size takes into account a maximum of 20% attrition over time, as well as clustering of data in schools and loss of power due to multiple imputation. Based on this power analysis, sample sizes need to be 662 adolescents per condition (alpha < .05, power = .80); at least 1,324 adolescents will be included.

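### Stratifying a small number of schools by educational level alone limits imbalance but does not ensure an even spread of level or 662 pupils per arm, and the analysis may leave the stratifier out

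*Protocol article*

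**What the plan says.** Under Design: "Randomization of schools, stratified by educational level, to either one of the conditions will be conducted by an independent statistician". The purpose follows: "Stratifying by educational level is needed to evenly distribute educational level across intervention and control group, despite the small number of schools". The article states no other constraint on the allocation.

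Under Participants and procedure the requirement is set in pupils: "sample sizes need to be 662 adolescents per condition (alpha < .05, power = .80); at least 1,324 adolescents will be included". Interested schools are not held to a fixed size: "they will be asked to participate with as many as possible second grade classrooms". The sample is meant to be diverse: "We will ensure inclusion of low SES and ethnic minority groups, as well as different educational levels".

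Under Data analysis, the arms are to be compared at baseline on depressive symptoms and on demographic variables, with school level and ethnic background among the examples. Variables whose distributions differ then enter every effectiveness model as confounders. SES is not among the examples, although the Parent measures section collects parental education, employment, working hours and salary.

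**The concern.** The unit that is balanced is not the unit in which the aims are stated. Stratified allocation evens out the number of schools per level. It does not even out pupils when schools differ in size, and a level with an odd number of schools cannot be split evenly. With few schools, such differences do not average out.

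The planned remedy also depends on what is observed. If educational level looks balanced, the factor that shaped the randomisation is left out of the model, which tends to cost precision. If it looks unbalanced, it goes in. With few schools, an observed difference is a weak guide to which covariates matter, because that depends mainly on how strongly they predict depressive symptoms. At stake are chance differences between schools that become mixed with the programme effect, and a model that is settled only after the baseline data have been seen.

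**Working it through.** **1. The plan's own figure.** The effect size is stated: the cited meta-analysis "indicated the significant average effect size to be 0.20 at 12-months follow-up with the CDI > 13 score as cut-off". Power .80 and 20% attrition are also stated. I read 0.20 as SD units and assume a two-sided alpha of .05.

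- n per arm = 2 × (1.96 + 0.842)² / 0.20² ≈ 393
- After attrition: 393 / 0.80 ≈ 492
- Factor left for clustering and imputation: 662 / 492 ≈ 1.346

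The article does not give the components of that factor, so 662 can be neither reproduced nor refuted. I take it as given.

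**2. Odd strata.** Suppose there are 12 schools of identical size, with 5, 4 and 3 schools in three levels, split 3:2, 2:2 and 1:2. The first level makes up 3/6 = 50% of one arm and 2/6 = 33% of the other, a gap of 17 points. Size plays no part in this.

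**3. Unequal school sizes.** The article gives no number of schools, strata or sizes, so these are assumptions: 1,324 pupils in total, one level per school, and a school-size coefficient of variation (CV) of 0.2 to 0.5. For 12 schools with four in each of three levels, simulated stratified allocation gives:

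| Size CV | Largest level gap ≥10 points | ≥20 points | Smaller arm below 596 (10% under 662) |
|---|---|---|---|
| 0.2 | 15% | 0.1% | 8% |
| 0.3 | 43% | 4% | 25% |
| 0.5 | 74% | 29% | 49% |

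Over 6 to 16 schools and 2 to 4 strata at CV 0.5, the median largest level gap is 8–27 points with stratification and 20–64 points without. The median smaller arm is 518–606 pupils. With CV 0.2 and even strata (8 schools in 2 strata, 12 in 2 or 3), the medians are 4–6 points and 631–636 pupils. With CV 0.2 but 8 schools in 3 strata, where odd strata are unavoidable, they are 21 points and 571 pupils.

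**4. SES and ethnic mix.** If these pupils were concentrated in a few schools (an assumption), and 12 schools split 6:6, then:

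- two such schools share an arm with probability 2 × C(10,4) / C(12,6) = 420 / 924 = 45%
- three all share an arm with probability 2 × C(9,3) / C(12,6) = 168 / 924 = 18%

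Over 6 to 16 schools the ranges are 40–47% and 10–20%.

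**5. Power at unequal arms, total fixed at 1,324.** Effective arm size m = pupils × 0.80 / 1.346, and power = Φ(0.20 / √(1/m₁ + 1/m₂) − 1.96).

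- 662/662: m = 393.5 each, power 0.801
- 596/728: m = 354.2 and 432.7, power 0.797
- 530/794 (1.5:1): m = 315.0 and 471.9, power 0.785
- 441/883 (2:1): m = 262.1 and 524.8, power 0.753

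**6. Would a better allocation help?** For a like-for-like comparison, odd strata were alternated so that the arms hold near-equal numbers of schools. With 12 schools and CV 0.3–0.5, drawing from a best-balanced subset cuts level gaps of 20 points or more from 4–50% to 1–9%, and smaller arms below 596 from 25–51% to 1–17%. These gains depend on the balance score. On rechecking, other reasonable weightings kept the direction but not always the size. A score dominated by arm size could leave level balance no better than stratification does.

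**The case against.** The strongest reply is that the Design sentence states a purpose, not a guarantee. It admits that schools are few and takes a recognised remedy, which reduced level imbalance in every scenario tested. That stands. A reader might infer that stratification cannot deliver the balance claimed. The documents do not support this: similar-sized schools in even strata come close to it.

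A reader might also infer that the trial recruits low-SES and minority schools that could all land in one arm. The article says "We will ensure inclusion of low SES and ethnic minority groups": groups, not schools. The 45% and 18% answer a hypothetical.

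A third tempting reading is that unequal arms leave the trial underpowered because "sample sizes need to be 662 adolescents per condition". The total of 1,324 is a minimum, so recruiting more pupils can bring both arms to 662. Even with the total fixed, a 1.5:1 split costs less than two points of power.

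Further, the number of schools, the strata and the block method may be in the full protocol, so their absence is no fault. Schools that teach several levels would show smaller gaps than those simulated. The baseline check names school level and ethnic background, which mitigates the problem.

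What survives is narrower. The stated rule balances schools while the aims are in pupils. SES, ethnicity and school size are not stated as constraints on allocation. Adjustment that depends on observed differences does not replace balance by design or a fixed covariate set.

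**Conclusion.** The point holds in a limited form. Stratifying by educational level is better than not stratifying. It does not by itself ensure an even spread of level among pupils or 662 pupils per condition, and the analysis rule may leave the stratifier out of the model.

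The loss of power is small. The concern is chance confounding between schools and programme, and avoidable loss of precision. How large the imbalance may be is uncertain: the chance of a 20-point level gap runs from about 0.1% to 50% across the 12-school settings above. Every such percentage rests on assumed school numbers, strata and sizes. The mismatch between schools and pupils, and the conditional adjustment rule, follow from the text without those assumptions.

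**What to change.** 1. **Analysis.** Include educational level, as the randomisation factor, in all effectiveness models whether or not the arms differ. Pre-specify baseline depressive symptoms, ethnic background and parental SES as covariates instead of choosing them by observed differences, and keep the number of school-level covariates small. No new data are needed, but missing parent questionnaires will leave gaps in SES that need a stated handling.

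2. **Allocation, if all schools are recruited before the draw.** Have the independent statistician use covariate-constrained randomisation on pupils per arm, share of pupils per educational level, and whatever school-level SES and ethnic mix is available. Fix the weights of the balance score in advance so that arm size does not dominate. Draw from a best-balanced subset large enough for a valid randomisation test, and include the constraint factors in the analysis. This needs no extra schools or pupils. It does need school-level counts, and recruitment must be complete before allocation.

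3. **Otherwise.** Reword the Design section to say that stratification is intended to limit, not remove, imbalance in educational level. This costs one sentence.

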**Figure 1 F1:**
[figure not shown]
**Study design**.

To test the (long term) effectiveness of the program, the outcomes will be assessed through self-report questionnaires approximately 1 month before the start of the program (baseline: T1), directly after the program (T2), and 6 (T3), 12 (T4), 18 (T5) and 24 (T6) months after the end of the program. Adolescents in the control condition will complete the questionnaires at exactly the same time points. Parental self-reports will be administered at baseline only. Adolescents assigned to the experimental condition will receive the OVK program, and adolescents in the control condition will receive care as usual (no program). As a reward for participation in the study, the schools in the control condition will receive a training for teachers in the OVK program between T3 and T4, on the strict condition that they will not provide the program to the adolescents who participated in the study.

OVK will be incorporated into the school curriculum; the 16-lesson program will be delivered once a week by trained psychologists to groups with a maximum of 15 adolescents. Incorporating the program in the school curriculum enables us to truly provide the program to all adolescents in a certain grade. As a result, high attendance rates will be assured and no stigmatization will occur. To keep the attrition rates at a minimum, all adolescents absent at a given measurement will be provided another possibility in the same time period to complete the questionnaire. Also, adolescents who leave school will be asked, with assistance of the school, to continue participating in the study. The trial is registered at the Dutch Trial Register: NTR2879.

### Participants and procedure

Participants will be adolescents in their second year of secondary school (8th grade, ages 12-14) [28]. Secondary schools in the southern and middle part of the Netherlands will be approached to participate in the study. Only adolescents in middle school grade 8 will be included. We will ensure inclusion of low SES and ethnic minority groups, as well as different educational levels (Dutch middle school prepares adolescents for vocational up to university level). The exclusion criterion consists of parental refusal of their child's participation in the study. When schools show interest, they will be asked to participate with as many as possible second grade classrooms. We expect that-once included in the study-across the entire study period, approximately 80% of adolescents will provide complete data [33,34].

A meta-analysis on 17 controlled studies on PRP indicated the significant average effect size to be 0.20 at 12-months follow-up with the CDI > 13 score as cut-off [28]. Power analysis (G-power) based on this 12-month mean effect size takes into account a maximum of 20% attrition over time, as well as clustering of data in schools and loss of power due to multiple imputation. Based on this power analysis, sample sizes need to be 662 adolescents per condition (alpha < .05, power = .80); at least 1,324 adolescents will be included.

With support from participating schools, parents of eligible adolescents will receive a letter, in which they will be fully informed about the study aims and procedure. For schools in the intervention condition a presentation will be held to inform parents and teachers about the content of the program and the study. Given that schools incorporate the program into their curriculum, passive consent will be obtained from parents. Each wave, adolescents will fill out a questionnaire in class during school hours. The 50-minute questionnaire will either be a web-based or a paper version, depending on the school's preferences. Parents fill out a 25-minute questionnaire at baseline only, addressing parental depression, anxiety, child and parental diagnostic status, and parenting skills. The mother will be asked to fill out the web-based questionnaire. Three weeks after the first mailing, non-responders will receive a reminder with the possibility to complete the questionnaire online or on paper. When not responding within 2 weeks, these parents will be contacted by phone. At any time, parents are free to withdraw themselves, and/or their child from the study. The Ethical Committee (ECG) of the Faculty of Social Sciences of the Radboud University Nijmegen has approved the study design and data collection.

